#### Provider Survey Data

The evaluation of the developed structures and processes of the project and the health care provider’s satisfaction (secondary outcomes 9 and 10 in Table 2) is based on provider survey data. These data were collected by interviewing all participants with a paper questionnaire. The aim is to evaluate if the processes and structures have been established as planned from the point of view of the participating providers. In this context, factors that promote or hinder the implementation of the project should be identified. All data will be collected completely anonymously, so that no conclusions can be drawn about the results of individual providers. Only an overall picture can be collected and compared. This analysis is part of the quality assurance and further development of the project.

#### Ambulatory Claims Data and Drug Prescription Data

To analyze secondary outcome 11, we use ambulatory claims data and drug prescription data. Ambulatory claims data are used to analyze the frequency of contact to ambulatory health providers. Therefore, the number of treatment cases will be compared to the need of a treatment. The question is if patients with more need of a treatment have higher numbers of treatment cases. A treatment case is defined as the sum of all medical services delivered by 1 physician during 1 quarter. Important diagnostic and therapeutic services for the NPPV patients will be defined and analyzed by checking if the patients receive these selected services and by computing the costs of ambulatory care. In addition, the analysis proves if the patients receive pharmacological care. It is analyzed whether they are under- or oversupplied. Within these analyses, patients who are part of the NPPV program are compared with patients who are not part of the NPPV program. The identification of patients who are part of the NPPV program is done by searching providers in the data who have billed NPPV services. When patients visit these providers, they are classified as an NPPV patient. The control group will be determined by using propensity score matching. The goal is to determine whether the treatment of the 2 patient groups differs and whether the program can improve the care of certain patient groups.

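### Outcome 11 assigns patients to the NPPV group by the same physician contacts it then counts, which can create an excess of treatment cases with no programme effect

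*Protocol article*

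**What the plan says.** The rule is in the protocol article, Data Analyses, under the heading Ambulatory Claims Data and Drug Prescription Data. It has two steps:

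- Providers are flagged: "The identification of patients who are part of the NPPV program is done by searching providers in the data who have billed NPPV services".
- Patients are then assigned through those providers: "When patients visit these providers, they are classified as an NPPV patient".

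The outcomes come from the same claims:

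- Contacts: "Ambulatory claims data are used to analyze the frequency of contact to ambulatory health providers".
- Counting unit: "A treatment case is defined as the sum of all medical services delivered by 1 physician during 1 quarter".
- Services and costs: the analysis proceeds by "checking if the patients receive these selected services and by computing the costs of ambulatory care".

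The stated question is a relation with need ("The question is if patients with more need of a treatment have higher numbers of treatment cases"), but the section also plans a comparison of groups: "patients who are part of the NPPV program are compared with patients who are not part of the NPPV program". On controls it says: "The control group will be determined by using propensity score matching".

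The section of the same name under Study Outcomes and Data Sources gives one data window, the first quarter of 2016 to the third quarter of 2020. It does not divide that window into a period for classification and a period for outcomes.

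**The concern.** Exposure is defined by a physician contact, and the main outcome is the number of physician contacts. Two things follow.

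1. The visit that makes someone an NPPV patient is itself at least one treatment case, and it carries a cost.
2. A patient who sees more physicians has more chances that one of them bills NPPV services, so the NPPV group over-represents heavy users.

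Both push the count in the NPPV group upwards whether or not the programme changes care. Propensity scores built on earlier characteristics balance expected use. They do not undo selection on the contacts actually made in the period being counted.

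Outcome 11 is the listed measure for the fourth research question (Study Design and Research Questions), which asks whether NPPV induces a more needs-based approach. An artefact of classification could be read as an answer to that question. The primary outcome is not affected: it uses the insurers' data on known participants, and its matching variables come from the 12 months before inclusion (Analyses in SHI Routine Data).

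**Working it through.** The article gives no expected difference or sample size for outcome 11, so there is no stated figure to reproduce. The check asks what the classification rule does when the programme has no effect.

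**Taken from the article:** the classification rule, the physician-quarter as counting unit, the single data window, and matched controls.

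**Assumed (not in the article):** how many physicians a patient sees, how contacts are spread over them, and the share of providers who bill NPPV services.

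**Step 1. Mechanism.** If a patient sees K physicians and each bills NPPV services with probability p, then P(classified NPPV | K) = 1 - (1 - p)^K. With p = 0.10 this is 10.0% for K = 1 and 1 - 0.9^3 = 27.1% for K = 3.

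**Step 2. Unmatched illustration.** Let K = 1 + Poisson(λ), so that everyone sees at least one physician. Each physician is seen in 1 to 4 quarters, mean 2.5. Write q = 1 - p.

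- P(not classified) = P0 = q·exp(-λp)
- Mean K if not classified = 1 + λq
- Mean K if classified = [(1 + λ) - P0(1 + λq)] / (1 - P0)
- Mean treatment cases = 2.5 × mean K

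Worked case, λ = 1 and p = 0.20: P0 = 0.8 × exp(-0.2) = 0.6550. Not classified: K = 1.80, or 4.50 cases. Classified: K = (2 - 0.6550 × 1.80) / 0.3450 = 2.380, or 5.95 cases. Ratio 1.32.

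| Mean physicians | p = 0.05 | p = 0.10 | p = 0.20 |
|---|---|---|---|
| 1.5 | 1.23 | 1.24 | 1.26 |
| 2 | 1.27 | 1.28 | 1.32 |
| 3 | 1.25 | 1.27 | 1.33 |

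The spurious excess is 23-33%. This compares unmatched groups, which is not the comparison the plan makes.

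**Step 3. With matching on prior use.** Simulation of 1,000,000 patients with no programme effect. Contacts are gamma-Poisson (shape 1.5; mean 2, 4 or 8 treatment cases per window), 10% or 30% of contacts or providers are NPPV, and patients are matched exactly on the prior-period case count as a stand-in for propensity matching. The true ratio is 1.00.

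| Design | Contacts spread over providers | One provider per patient |
|---|---|---|
| Same window, controls may have no visit | 1.32-2.35 | 1.02-1.31 |
| Same window, controls have at least 1 visit | 1.31-1.83 | 1.00 |
| Outcome in a later window, controls have at least 1 visit | 1.13-1.27 | 1.00 |

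Another gamma-Poisson run gave 1.28-1.50 after prior-use matching in the same window and 1.06-1.15 when outcomes were counted only after classification. In the Step 2 model with mean 2 physicians, matching on a prior physician count that stays the same in 80% of patients leaves an excess of 8-11%.

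**Step 4. Need gradient.** In the Step 2 model, treat mean 1.5 physicians as low need and mean 3 as high need. For p = 0.05 the excess is 4.54 - 3.69 = 0.85 cases at low need and 9.03 - 7.25 = 1.78 at high need. For p = 0.20 it is 4.41 - 3.50 = 0.91 and 8.66 - 6.50 = 2.16. The apparent gradient from low to high need is therefore 4.25-4.49 cases in the NPPV group against 3.00-3.56 in the others, without any effect. On the ratio scale the excess hardly changes with need (1.23-1.26 against 1.25-1.33).

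**The case against.** The strongest reply is that the comparison is matched. Among patients with the same number of physicians, the Step 2 model gives a ratio of 1.00, and good matching on stable prior use shrinks the excess. This stands in part. The percentages in Step 2 should not be read as the bias of the planned analysis, and it would be wrong to say that the controls have fewer physicians by construction, because the controls are a matched set. But the number of physicians in the outcome period is not a prior characteristic, and matching on prior use left an excess in every run where contacts were spread over several providers.

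Second, the article is condensed. Index dates, matching variables and follow-up windows may be set out in a fuller plan, and their absence here is not itself an error. The point rests instead on what is stated: a visit-based assignment rule applied to the same claims in which visits are the outcome.

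Third, patients may stay with one relevant provider, and controls probably have at least one contact too, since the claims carry coded outpatient diagnoses. If both hold, the ratio is 1.00. The article does not settle this. Its description of the intervention as a network of neurologists, psychiatrists and psychotherapists makes contact with several providers plausible.

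Fourth, the stated question is about need and treatment cases, not about level. A reader might infer that the artefact looks exactly like needs-led care. That is not shown: the absolute gradient steepens in one unmatched model, the relative one barely moves, and the article fixes neither the scale nor the measure of need.

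**Conclusion.** The concern holds as a risk built into the stated rule. Where patients see several providers, group membership depends on the outcome process. An excess of treatment cases can then appear in the NPPV group with no programme effect, and propensity matching on earlier characteristics does not generally remove it.

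A reader might go further and infer that NPPV patients are bound to show more contacts and costs even if the programme does nothing. The document does not support that. Null ratios ran from 1.00 to 2.35 depending on provider loyalty, the definition of controls and the window, none of which the article fixes. The 23-33% is unmatched and illustrative only. Costs were not simulated; an excess there follows only if costs rise with contacts.

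This is a different problem from counting non-enrolled visitors as NPPV patients. That would dilute a true effect, whereas this can create one, and it would remain even if every visitor were enrolled.

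The consequence is confined to one secondary outcome. It should be corrected because that outcome is the listed measure for the fourth research question.

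**What to change.** 1. Give each NPPV patient an index quarter: the first quarter with an NPPV service billed for that patient, if the claims show it; otherwise the first visit to an NPPV-billing provider.
2. Give each control an index quarter from a comparable visit to a non-NPPV provider of the same specialty in the same calendar quarter.
3. Match on treatment cases and distinct physicians in the four quarters before index. With claims from the first quarter of 2016 and enrolment from December 2017, these quarters are available.
4. Count treatment cases, services, prescriptions and costs only from the quarter after index, over the same number of quarters in both groups.

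**Cost.** The claims are already held and linked, so no new data are needed. The Results section reports that data analysis was completed in the first half of 2022, so this is a re-analysis, or a sensitivity analysis reported beside the original.

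**Downside.** The index quarter drops out of the outcome, as do patients without later observed quarters. With data ending in the third quarter of 2020, four follow-up quarters exist only for index quarters up to the third quarter of 2019. Moving the outcome to a later window reduced the spurious ratio in the simulations to 1.06-1.27 where contacts were spread over providers, not to 1.00. Residual confounding by unmeasured need remains and should be stated with the result.

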### Ethics Approval

Ethics approval for this trial was obtained from the ethics committee of the chamber of physicians in North Rhine (September 13, 2017, reference No 2017287).

## Results

Enrollment of physicians, therapists, and patients is completed. Data analysis was completed in the first half of 2022, and the results will be disseminated through scientific publications, academic conferences, and particularly a publicly available report to the German Federal Joint Committee. This report consists of a comprehensive summary over the study and a detailed description of all evaluation methods and corresponding results. The report is expected to be available after review by the German Federal Joint Committee in the first half of 2023 and can be found on the internet [31].

## Discussion

### Overview and Perspectives

This paper describes the protocol for a prospective cohort trial to evaluate the effects of the NPPV program. This program is unique and the first intervention to offer a low-threshold access for both mental and neurological diseases, implement a stepped model of care organized according to patients’ medical needs, and it builds up on a strong network of multiprofessional health care providers in Germany. We expect that NPPV will in particular reduce costs of illness, improve quality of care, and increase patient and provider satisfaction.

The Act to strengthen care in SHI (“GKV-Versorgungsstärkungsgesetz”) from 2015 included a structural reform of outpatient psychotherapy, which came into effect in 2017 [32]. While this reform improved the access to outpatient psychotherapeutic care [9], several evidence-practice gaps in the treatment of mental and neurological diseases prevail. We expect the consequences of the COVID-19 pandemic to further increase the medical and socioeconomic burden of both mental and neurological diseases and enhance the pressure on health care systems [33]. The NPPV program is designed to face these challenges and improve access to and quality of care. While there are several projects funded by Innovation Fund, which focus on mental or neurological diseases, most of them focus on selected settings, specific diseases, health care sectors, or treatment methods [13]. Section 92 of Book V of the German Code of Social Law (§92 SGB V) specifies that regulations on a multiprofessional, coordinated, and structured care for patients with severe mental diseases are to be established in order to advance the German health care system. Several elements of the NPPV program are part of this advancement.

### Strengths and Limitations

Our study has some strengths. We include 14,000 patients over 7 indication groups and analyze several different data sources (both primary and routine data). We also consider perspectives of patients, providers, and SHI in our analysis. Taken together, this enables a comprehensive evaluation of the NPPV program for patients with a wide range of mental and neurological diseases. However, our study also has some limitations. First, although we use matched control groups for the patient survey and analysis of routine data, our evaluation has a nonrandomized design. Second, we cannot completely rule out differences in disease severity between intervention and control groups. While an acutely higher disease severity increases the likelihood of being included in the program, this characteristic is not reflected in routine data used for our matching procedure. Third, we may face a selection bias in the patient survey as patients who are younger, healthier, and more educated are more likely to be willing to participate in our study. Finally, long-term effects (>24 months) on costs and patient outcomes cannot be evaluated in our analyses.

## Appendix

Multimedia Appendix 1 Questionnaires patient survey.

Multimedia Appendix 2 Questionnaires provider survey.

Multimedia Appendix 3 Confirmation government funding and assessment corresponding to a peer-review.

## Abbreviations

GBA: German Federal Joint Committee
ICBT: internet-based cognitive behavioral therapy
ICD: International Statistical Classification of Diseases and Related Health Problems
NPPV: Neurologisch-psychiatrische und psychotherapeutische Versorgung
SHI: statutory health insurance
